### Outcomes

PCP outcomes will include primary objective 1 and a number of secondary outcomes (Table 2 and Fig. 3). The primary outcome is the Social Distance Scale (SDS), which is a commonly used measure of stigma [42, 78, 79]. The SDS was developed in the 1920s by Bogardus [42] to measure the level of acceptability of various types of social relationships between Americans and members of common ethnic groups [78, 112]. The modified SDS has been widely used to measure mental health-related stigma [78, 113]. The SDS measures the acceptability of different degrees of social distance and thus, by inference, the attitude of the respondent to the person with the condition [114]. A commonly used version consists of questions that represent social contact with different degrees of distance, such as renting a room to someone with a condition under study, working in the same place, marrying one’s child to a person with the conditions, or engaging someone in child care. The SDS sum score represents the attitude of the respondent toward the condition. The SDS has been adapted for use both with and without vignettes, using a 6-point scale and 12 items. Cross-cultural use of SDS in LMIC across health conditions has recently been reviewed [115]. In this trial, PCPs will be presented with 3 versions of the SDS, in random order. Each version includes a vignette followed by 12 questions regarding willingness to engage with the person in the vignette. These 12 questions have been culturally adapted for Nepal and other LMICs [116]. The three vignettes represent persons with depression, psychosis, and alcohol use disorder. Of note, an SDS vignette for generalized anxiety disorder was not added in addition to depression, given that the current three vignettes cover common mental health conditions, severe mental health conditions, and substance use conditions. Moreover, it would add to respondent burden in terms of additional questions and may lead to respondent inattention given the repetition of the same questions multiple times.

**Table 2 Tab2:** Study measures

Domain	Tool
**Primary care providers (PCPs)**	
Attitudes	*Social Distance Scale (SDS)*^A, C^: explicit stigmatizing attitudes questionnaire [42] widely used in mental health [78] in global stigma comparisons [79]; the Nepali version has 12 self-report questions on a scale of 1 to 6 and three vignettes (depression, psychosis, and alcohol use disorder); Nepal *α* = 0.90. ***Primary outcome for objective 1; mediator for objective 2***. *PCP*_*T0,T1,T2,T3*_.
	*Implicit Association Test (IAT)*^B^: implicit biases against mental illness; tablet-administered test: mental health version has been used in numerous high-resource settings [80–83]; in Nepal, we developed two versions: mental illness vs. harmfulness and mental illness vs. burdensomeness; administration time is 15 min. *PCP*_*T0,T1,T2,T3*_.
Behavioral intentions	*Reported and Intended Behavior Scale (RIBS)*^B^: 8-item scale to measure the behavioral intentions towards people with mental health problems [84]. *PCP*_*T0,T1,T2,T3*_.
Knowledge	*mhGAP Knowledge*^B, C^: 31 multiple-choice questions for diagnostic and treatment knowledge; globally used for mhGAP trainings [85–87]. *PCP*_*T0,T1,T2,T3*_.
Competency and quality	*Enhancing Assessment of Common Therapeutic factors (ENACT)*^B, C^: observed structured clinical exam; health workers conduct a 10-min role-play with standardized patients; 15 items for common factors, 5 items for mhGAP assessment competencies, and 2 items for recommended diagnosis and treatment; developed in Nepal [88, 89]; *α* = 0.89; administered through the World Health Organization Ensuring Quality in Psychological Support (EQUIP) platform [90]. *PCP*_*T0,T1,T2,T3*_.
Self-efficacy	*mhGAP Clinical Self-Efficacy*^B^: 38 self-reported ability to diagnose and treat mental illness; standard mhGAP assessment; widely used globally [85–87]; Nepal *α* = 0.99. *PCP*_*T0,T1,T2,T3*_.
**Patient**	
Accurate diagnosis	*Structured Clinical Interview for DSM-5-Clinical Trials Version (SCID-5-CV)*^A^: psychiatrist interview for diagnostic accuracy [91]; SCID for DSM-IV previously used in Nepal showing strong concordance with Composite International Diagnostic Interview [92]; accurate diagnosis is used as a proxy for reach of services. ***Primary (implementation) outcome for objective 2***. *PT*_*T1*_.
Functioning	*WHO Disability Assessment Schedule (WHODAS)*^B^: self or caregiver report of functional impairment with 13 fixed response questions and 3 open-ended related timing [93]; widely used in Nepal [61, 70, 94–96]; Nepal *α* = 0.87. *PT*_*T0,T1,T2*_.
Quality of life	*EQ-5D-5L*^B^: 5-item self or caregiver report of quality of life years (QALYs) based on 5 dimensions: mobility, self-care, daily activities, pain/discomfort, and mood (anxiety/depression); official EuroQol translation available for Nepal; Asian utility weights available from Thailand [97]. *PT*_*T0,T1,T2*_.
Psychiatric symptom severity	*Patient Health Questionnaire (PHQ9)*^B^: 9-item assessment of depression symptoms and 1-item impact on functioning [98]; validated in a primary care setting in Nepal, with the addition of a local idiom of distress “heart-mind problems” [67]; validated Nepal cutoff ≥ 10: sensitivity = 94%, specificity = 80%; *α* = 0.84. *PT*_*T0,T1,T2*_.
	*Generalized Anxiety Disorder (GAD-7)*^B^: 7-item assessment of anxiety symptoms, structured in the same format as the PHQ-9. Previously used in Nepal [99–101]. *PT*_*T0,T1,T2*_.
	*Positive and Negative Syndrome Scale (PANSS)*^B^: assessment of positive and negative symptoms of psychosis, designed for schizophrenia symptom severity [102]; in Nepal, adapted for self- or caregiver report [94], adapted scoring cutoff > 10, sensitivity = 90%, positive items *α* = 0.82, negative items *α* = 0.88; combined *α* = 0.89. *PT*_*T0,T1,T2*_.
	*Alcohol Use Disorder Identification Test (AUDIT)*^B^: 13-item assessment of the quantity of alcohol consumption, tolerance, and dependence [103]; validated in a medical setting in Nepal [104]; cutoff ≥ 9, sensitivity 96.7% for males and 94.37% for females, specificity 79.6% and 85.4%, respectively; *α* = 0.82. *PT*_*T0,T1,T2*_.
Competency of provider	*Enhancing Assessment of Common Therapeutic factors (ENACT)-Patient version*^B^: 12-item patient version of the ENACT scale that allows patient and/or caregiver to comment on therapeutic rapport, comprehensiveness of mental health evaluation, and communication skills; developed in Nepal and shown to associate with depression treatment outcomes [105]. This is also an indicator of a positive experience of care [106]. *PT*_*T2*_.
Stigma and discrimination	*Discrimination and Stigma Scale Short Version (DISCUS)*^B^: 11-item scale to measure discrimination and stigma experienced by people with mental health problems [107]. *PT*_*T2*_.
	*Internalized Stigma of Mental Illness (ISMI)*^B^: 29-item scale used to measure internalized stigma among people with mental health problems [108]. *PT*_*T2*_.
Barriers to care	*Barriers to Access to Care Evaluation (BACE)*^B^: stigma and other barriers to accessing health services [109], adapted and used in rural Nepal *n* = 324 [47]. *PT*_*T2*_.
Cost of care	*Client Service Receipt Inventory (CSRI)*^B^: costs associated with psychiatric interventions [110]; records information on employment earnings and benefits, hospital care, primary care, social care, and support from informal caregivers (e.g., family); previously used in Nepal [111]. The period covered for costs will be from enrollment in the health facility onward until the assessment point (i.e., 0–3 months; 3–6 months). *PT*_*T1,T2*_.

Study objectives: ^A^primary outcome, ^B^secondary outcome, and ^C^mediator. Assessment time points. Primary care providers: *PCP*_*T0*_ = pre-training, *PCP*_*T1*_ = post-training, *PCP*_*T2*_ = 3-month follow-up, *PCP*_*T1*_ = 6-month follow-up. Patients: *PT*_*T0*_ = screening in primary care, *PT*_*T1*_ = 3-month follow-up, *PT*_*T2*_ = 6-month follow-up

**Fig. 3 Fig3:**
[figure not shown]
Data collection pathway for primary care providers (PCPs) and patients (PT) in primary care facilities. Abbreviations: mhGAP, mental health Gap Action Programme; RESHAPE, Reducing Stigma Among Healthcare Providers; IAU, implementation as usual

Secondary outcomes at the PCP level for objective 1 include the Reported and Intended Behavior Scale (RIBS), which is a measure of behavioral intentions [84]; PCP knowledge about mental health conditions and their treatment, as assessed with selected questions from the mhGAP knowledge test [85–87]; clinical skill as assessed with a structured role play that is rated with the Enhancing Assessment of Common Therapeutic factors (ENACT) [88, 89], an observational tool with 15 competencies linked to “common factors” for good quality psychosocial care; and a supplementary competency assessment for 5 mhGAP competencies. In addition, after each structured role play, PCPs are asked about what diagnosis and treatment they would recommend for the standardized patient. In addition to explicit stigma, we will measure implicit stigma with the Implicit Association Test (IAT) adapted for Nepal [11]. A self-report of clinical self-efficacy is also collected [85–87].

The patient-level data will be evaluated in objective 2, which includes the implementation-effectiveness component. The primary implementation outcome is *reach*, operationalized as the accuracy of diagnosis. This will be established by recruiting patients from primary care facilities during months 4–6 post-training. The patients visiting the health facility will be evaluated by PCPs. After PCP evaluation, a researcher stationed in each health facility will screen the consenting patients with locally validated tools for PHQ-9 [67] for depression, the Generalized Anxiety Disorder (GAD-7) for anxiety, a version of the Positive and Negative Syndrome Scale (PANSS) [94] previously adapted for self or caregiver report in Nepal (the Nepali version includes screening items before proceeding to the 14 items), and the Alcohol Use Disorders Identification Test (AUDIT) [104].

If the person is identified by the PCP as having a mental health condition, the patient will be recruited for follow-up at the 3-month period. Similarly, a subset of patients visiting health facilities who are *not* detected as having mental health conditions by PCPs will be randomly selected and asked to participate as well. This will include a selection of both patients who score above and below screening cutoffs, with over recruitment of those screening above cutoffs, as they are more likely to have a missed diagnosis.

At 3 months after patient enrollment, a psychiatrist will complete a remote structured clinical interview using the Structured Clinical Interview for DSM-5-Research Version (SCID-5-RV) [91], including the modules for depression, generalized anxiety, mania, schizophrenia, and alcohol use disorder. The 3-month period between PCP diagnosis and psychiatrist SCID evaluation is because PCPs may do an initial assessment and then ask a patient to return in a few weeks to confirm the diagnosis. Therefore, PCPs have a 3-month window to confirm or revise their clinical diagnoses. The last recorded clinical diagnosis of the 3-month period will be the one compared against the psychiatrist’s SCID outcome.

In the SCID, each mental health condition includes screening questions, and if screening questions are positive, the psychiatrist proceeds to a full battery for that module to make diagnoses according to the DSM-5 criteria. Of note, co-morbidities can be identified if participants meet the criteria for multiple disorders. From a feasibility perspective, it is not possible for psychiatrists to conduct a SCID on every patient seen by PCPs in a 3-month period. Therefore, the SCID interviews will be performed with all patients who received a mental health diagnosis by a PCP, as well as a subset of patients who did not receive a diagnosis, as mentioned above (see Fig. 4).

**Fig. 4 Fig4:**
[figure not shown]
Data collection pathway for primary care providers (PCPs) and patients (PT) in primary care facilities. Abbreviations: mhGAP, mental health Gap Action Programme; RESHAPE, Reducing Stigma Among Healthcare Providers; IAU, implementation-as-usual. *Note*: Because our study can only recruit a subsample of those who do not receive a PCP diagnosis (estimated to be 40% in both arms) and 3-month follow-up can only include sub-samples of recruited patients who did not receive a diagnosis from a PCP (expected to be 10% of those who are true negatives and 50% of those who are false negatives), the between-arm comparison applies to a population which, compared to the general health facility-visiting population, has an overrepresentation of those who screen positive (yellow color participants at 3 months in the figure)

The psychiatrist is masked to the PCP diagnosis at the time of the SCID interview. After the SCID interview, the psychiatrist’s diagnosis will be used to categorize each patient into one of four groups: “true positives” = those patients who have the same diagnosis by the PCP and on the SCID; “false positives” = those patients who have a PCP diagnosis that is not confirmed on the SCID; “false negatives” = those patients who did not receive a PCP diagnosis, but who did receive a diagnosis on the SCID; and “true negatives” = those patients who were not diagnosed by a PCP and who did meet the criteria for any diagnosis on the SCID. We anticipate screening approximately 5500 patients in the primary care facilities and having approximately 1100 evaluated in SCID interviews by the psychiatrist. See Additional file 1: Fig. S3 for the estimated breakdown for recruitment based on categorization for the estimated breakdown for recruitment based on categorization according to PCP diagnoses, SCID interview outcomes and assumed sampling fractions. See Additional file 1 for details on *secondary outcomes*.

The participant timeline for PCPs and patients provides full details on when all instruments are administered (see Additional file 1: Table S1). Instruments have been piloted with PCPs and patients, and the time needed for completion at different time points was deemed feasible and acceptable to participants in the pilot cRCT.

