### Objectives

The cRCT has two co-primary objectives. Primary objective 1 is to determine the effect of the RESHAPE implementation strategy on stigma among PCPs (see Additional file 1: Fig. S1). This objective evaluates the attitudinal change among PCPs. *Hypothesis:* PCPs in the RESHAPE arm will have a greater reduction in stigma toward people with mental illness 6 months after training compared with primary care workers exposed to the standard training in IAU.

Primary objective 2 is to evaluate the effect of the RESHAPE implementation on reach. In the Reach Effectiveness-Adoption Implementation Maintenance (RE-AIM) framework [43–45], “*reach* is the number, proportion of the intended audience, and the representativeness of participants compared with the intended audience” [46]. Reach will be operationalized as the accuracy of diagnosis among PCPs. *Hypothesis*: PCPs in the RESHAPE arm will have greater reach in terms of a greater proportion of patients accurately diagnosed compared to IAU.

Primary objective 2 is a type 3 *implementation-effectiveness* objective because the implementation outcome (reach) is the primary focus. The effectiveness component, which is secondary, addresses an intervention at the patient level that is the same in both arms (i.e., mhGAP-IG recommended pharmacological and psychological treatments, see Table 1). It is only the implementation strategy with regard to how PCPs are trained which differs between the arms (implementing training-as-usual vs. RESHAPE). Therefore, one of the secondary objectives relates to the effectiveness of the care delivered. We hypothesize that RESHAPE will have non-inferior outcomes compared to IAU, i.e., a non-inferiority hypothesis. We have selected a non-inferiority approach because prior research in Nepal showed that, 6 months after training, PCPs delivered minimally adequate care for 94% of patients with depression and 95% of patients with alcohol use disorder [10]. Therefore, it is unlikely to improve upon this outcome when using RESHAPE, we thus want to test if the treatment outcomes are comparable across arms. This echoes the point raised above that detecting who needs care appears to be a bigger challenge than providing the right care once appropriate persons are identified.

**Table 1 Tab1:** Intervention and implementation elements for implementation as usual (IAU) vs. RESHAPE

	Implementation as usual (IAU)	RESHAPE implementation

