### Sample size

The cRCT was designed with a minimum of 80% power for each of the two co-primary PCP outcomes (objective 1: stigma; objective 2: reach), respectively, at an overall 5% significance level. Given that we will consider RESHAPE a meaningful implementation strategy under the condition that both co-primary outcomes are statistically significant, we assumed a 5% two-tailed significance level for each outcome and calculated power using a closed-form sample size formula [120] that assumes that the generalized estimating equations (GEE) approach will be used for the analysis (identity link for stigma and log link for reach). For the purposes of these power calculations, we assumed the following sample sizes at each of the four levels: 24 municipalities randomized to one of two implementation arms (RESHAPE vs. IAU), 3 health facilities per municipality (72 in total), and 3 PCPs per health facility (of the total of 216, we assume 80% will provide data for objective 1 analyses at the 6-month timepoint).

For objective 2, we estimate that 1 PCP will deliver mental health services per facility (a total of 72 PCPs), and each will recruit approximately 80 patients (total approximate sample 5760), of which approximately 16 are followed up at 3 months (total 1152, see Additional file 1: Fig. S3). We note that, in practice, some health facilities may have more than 1 PCP who delivers MH services. Sensitivity analyses show that power is still high in this case when the 80 patients are divided between 2 or more PCPs (see Additional file 1: Table S2 and Table S3). See Additional file 1 for additional details on the *sample size, including assumptions on correlation parameters*.

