### Statistical methods for primary and secondary outcomes

The main analysis of our two co-primary outcomes will be based on the intention-to-treat principle whereby all PCPs (objective 1 stigma) and all participants (objective 2 accurate diagnosis) will be included in the analysis in the study arm to which they were randomized irrespective of whether they complied with the assigned allocation of their municipality to one of the two implementation strategies (IAU and RESHAPE). Each analysis will be performed within the GEE framework paired with the matrix-adjusted equations (MAEE) approach [121] with identity link for stigma and log-link for reach (i.e., accuracy). MAEE is an approach whereby a set of estimating equations is posited for the correlation parameters just as estimating equations are used for the outcome model to estimate the impact of the RESHAPE implementation strategy. Importantly, MAEE provides confidence intervals for pairwise correlation parameters, which is particularly useful for the planning of future studies. Corrections such as the Kauermann-Carroll adjustment to variance estimates will be used to avoid “small-sample” bias that may arise given that fewer than 40 clusters (i.e., municipalities) are randomized [120, 122].

The model for each outcome will include the implementation arm, the covariates included in the constrained randomization procedure, and a set of PCP covariates identified a priori as potential confounders (e.g., age, gender, and health worker qualification level). If additional important covariates are identified post hoc, additional sensitivity analyses will add those covariates to the model, particularly if they are, by chance, imbalanced between arms. Please see Additional file 1 for additional details on the *statistical methods* as well as details on the *methods in analysis to handle protocol non-adherence and any statistical methods to handle missing data*, *interim analyses*, *methods for additional analyses*, *access to data and statistical code*, *data management*, and *dissemination plans*.

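### SCID sampling for the reach co-primary depends on the PCP's own diagnosis, so the sampled case mix can differ by arm and an unweighted accuracy ratio would be distorted

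*Protocol article*

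**What the plan says.** Under Objectives, the reach hypothesis for RESHAPE is "a greater proportion of patients accurately diagnosed compared to IAU". Trial design says the study is powered for total accuracy across conditions.

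Under Outcomes, "the SCID interviews will be performed with all patients who received a mental health diagnosis by a PCP, as well as a subset" of those without a diagnosis, with patients above the screening cutoffs deliberately over-recruited. The Fig. 4 note gives the planning figures: about 40% for recruitment of undiagnosed patients, the same in both arms, then 3-month follow-up of about 10% of the true negatives and 50% of the false negatives among them. It draws one consequence: "the between-arm comparison applies to a population which, compared to the general health facility-visiting population, has an overrepresentation of those who screen positive".

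On analysis, "Each analysis will be performed within the GEE framework paired with the matrix-adjusted equations (MAEE) approach", with a log link for reach, and with arm, the randomization covariates and PCP covariates in the model. Sampling weights are not mentioned. Further statistical detail is referred to Additional file 1.

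**The concern.** A caveat about over-represented screen-positives is a caveat about generalizability. It is sufficient only if both arms are enriched in the same way, and this sampling rule does not ensure that. Whether a patient enters the SCID sample depends on the PCP's diagnosis, which is made after randomization and is the behaviour that RESHAPE is meant to change.

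When a PCP detects a case that would have been missed, that patient moves from a stratum followed up at 50% to one followed up at 100%. When a PCP wrongly diagnoses a healthy patient, that patient moves from 10% to 100%. Equal sampling fractions in the two arms do not remove this, because the arms fill the strata differently.

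The sampled accuracy ratio then reflects the sampling fractions and how often PCPs diagnose, as well as how accurate they are. Sample size makes success conditional on both co-primaries being significant, so a distorted reach ratio bears directly on the trial's conclusion.

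**Working it through.** **The plan's own figures.** Sample size: "each will recruit approximately 80 patients (total approximate sample 5760), of which approximately 16 are followed up at 3 months (total 1152". 24 municipalities × 3 facilities × 1 PCP = 72; 72 × 80 = 5760; 72 × 16 = 1152; 1152/5760 = 20%. These reproduce exactly. Reach power cannot be reproduced, because the article gives no effect size or correlations.

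**Inputs from the plan.** Sampling fraction 1 for PCP-diagnosed patients; f_FN = 0.50 and f_TN = 0.10 on the recruited base. If the 40% is a prior sampling stage, then f_FN = 0.40 × 0.50 = 0.20 and f_TN = 0.40 × 0.10 = 0.04 on the base of all attenders. The wording allows either reading, so both are shown, the second in square brackets.

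**Assumed inputs.** Prevalence, sensitivity and specificity, none of which the article gives for this sample. The four conditions are collapsed into one 2×2 table, and clustering is ignored.

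**Formulas.** With TP = prev × sens, FN = prev × (1 − sens), FP = (1 − prev)(1 − spec) and TN = (1 − prev) × spec:
- accuracy before sampling = TP + TN
- sampled accuracy = (TP + f_TN·TN) / (TP + FP + f_FN·FN + f_TN·TN)

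**1. Sensitivity 30% vs 60%, specificity 95%, prevalence 20%.**
- IAU: TP 0.06, FP 0.04, FN 0.14, TN 0.76. RESHAPE: TP 0.12, FP 0.04, FN 0.08, TN 0.76.
- Before sampling: 0.82 vs 0.88, ratio 1.07.
- Sampled: (0.06 + 0.076)/(0.06 + 0.04 + 0.07 + 0.076) = 0.136/0.246 = 55.3%, against (0.12 + 0.076)/(0.12 + 0.04 + 0.04 + 0.076) = 0.196/0.276 = 71.0%. Ratio 1.28 [57.1% vs 72.9%, ratio 1.28].
- Diseased share of the sample: 0.13/0.246 = 53% vs 0.16/0.276 = 58% [56% vs 66%]. The mixtures differ by arm.
- Much of the rise above 1.07 would come from shared enrichment alone. At a fixed mix of 50% diseased, accuracy is 0.625 vs 0.775, ratio 1.24. This example therefore shows the total shift; the next one isolates the arm-dependent part.

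**2. Sensitivity 50% vs 60%, specificity 97% vs 94.95%, prevalence 17%.** (17% is the article's depression figure for primary care facilities, borrowed here.)
- Before sampling: 0.890 in both arms, ratio 1.00.
- Fixed enriched mixes favour RESHAPE: ratio 1.02 at 30% diseased, 1.05 at 50%.
- Sampled: 0.711 vs 0.704, ratio 0.991 [0.737 vs 0.706, ratio 0.959].

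The sampled ratio lies on the opposite side of 1 from these fixed mixes. Over-representation common to both arms cannot produce that.

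**3. Sensitivity 34.5% vs 72.5%, specificity 97% vs 90%, prevalence 17%.** (The pilot accuracies, used only as an assumed sensitivity pair.) Ratio before sampling 1.008; sampled 1.027 [0.948]. The direction depends on how the 40% is read.

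**4. Identical sensitivity and specificity in both arms.** The ratio is exactly 1 before and after sampling under either reading, given equal prevalence and equal sampling fractions.

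**Effect of weighting.** On the recruited base the inverse fractions are 1, 2 and 10. For IAU in case 1 the numerator is 0.06 + 10 × 0.076 = 0.82 and the denominator is 0.06 + 0.04 + 2 × 0.07 + 10 × 0.076 = 1.00, which returns 0.82. In practice the weights must come from PCP diagnosis by screen result, because true- or false-negative status is unknown before the SCID.

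**The case against.** The article never says that the reach model is unweighted. It sends further statistical methods and the assumed sampling fractions to Additional file 1, and an article may properly leave weights to the full plan. This stands: an unweighted analysis is an inference from the Fig. 4 note, which places the comparison in the sampled population, and from a model description without weights.

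The authors also disclose the fractions and the enrichment, and they nowhere name accuracy among all attenders as the target. That answers a charge of concealment. It does not rescue the note, because the sample is not one population common to both arms.

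A reader might infer that the design yields false rejections when training does nothing. It does not: case 4 gives a ratio of exactly 1. Settings can be built in which total accuracy is equal and the sampled ratio is not, but there sensitivity and specificity both differ and happen to cancel, so they are not cases of no training effect. They are also unstable. At 20% prevalence, sensitivity/specificity of 20%/97% vs 50%/89.5% gives a sampled ratio of 1.06 [0.99], and 10%/99% vs 70%/84% gives 1.13 [1.01].

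A reader might equally infer a bias that systematically favours RESHAPE. Cases 2 and 3 show that the direction is not fixed.

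**Conclusion.** The concern holds in a conditional form. SCID inclusion depends on a post-randomization variable that the training targets. If the arms differ in sensitivity or specificity, their SCID samples are different mixtures, and an unweighted accuracy ratio is distorted. The Fig. 4 note understates this whatever the analysis does.

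The size and direction cannot be fixed from the article. In the illustrations the ratio moved from 1.07 to about 1.28 under either reading of the fractions, and from 1.00 to 0.991 or 0.959. These are not forecasts. Case 1 on the recruited base implies 2,880 × (0.246 + 0.276) ≈ 1,503 interviews, against the planned 1,152. Type I error under no training effect is not inflated. That the primary reach model is unweighted is probable rather than established while Additional file 1 is unseen.

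**What to change.** 1. Log each patient's selection probability at enrollment, by index PCP diagnosis × screen status × facility. Use the index diagnosis, because the diagnosis scored against the SCID is the last one recorded within 3 months and may differ from the one that governed selection.
2. Prespecify inverse-sampling-probability-weighted GEE/MAEE estimates of total accuracy, and of sensitivity and specificity by arm. State which quantity reach is meant to capture, since the article's rationale is about detection while its power is for total accuracy.
3. Report the unweighted ratio beside them as a sensitivity analysis.
4. Correct the Fig. 4 note to say that the sampled mix can differ by arm, and clarify what the 40% refers to.
5. Restate the reach power for the weighted estimator. The plan claims "a minimum of 80% power for each of the two co-primary PCP outcomes", and that figure may not carry over.

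No new patients or procedures are needed, only one logged variable and revised analysis text. The real cost is precision: weighted total accuracy will have a wider interval, because a few heavily weighted true negatives carry much of the estimate. If Additional file 1 already specifies such weights, only the Fig. 4 note needs correcting.
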